#### Sedentary lifestyle

2.6.3

The sitting time (min/wk) will be assessed using the ActivPal device. ActivPAL has been proven to be a practical, reliable, and valid instrument for objectively recording sedentary activity.^[49]^ This device will be adhered to the front of the thigh of each participant, between the knee and the trunk, using an adhesive strip. Participants will use the devices for 7 days at each follow-up visit (baseline, 3, and 12 months). This device is used to estimate the average minutes of activity per day, average minutes spent sitting per day, and average number of steps per day. We will use cut-off points for the categorization of the sedentary behavior (0–5 counts/15 s) collected through the ActivPal devices, as proposed by Atkin et al.^[50]^

#### Caloric intake

2.6.4

Caloric intake (kcal/d) and dietary habits of participants will be evaluated using a semi-quantitative food-frequency questionnaire previously validated in Spain.^[51]^ The estimated frequency corresponds to the previous year at the time of the interview and is based on the typical portion sizes multiplied by the consumption frequency for each food. This value is then divided into 9 intake categories ranging from never to >6 servings/d. This will be used to estimate daily intake of macro- and micro-nutrients. Adherence to the Mediterranean diet will be assessed using the validated 14-point Mediterranean Diet Adherence Screener (MEDAS),^[52]^ developed by the PREDIMED study group, which explores compliance with various aspects considered characteristic of the Mediterranean diet. Adequate adherence will be assumed when the total score is 9 points or higher.

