### Procedures

2.5

Each participant will complete an initial visit and 2 follow-up visits at 3 and 12 months after study initiation (Fig. 1). Baseline data will be collected by a research nurse. The IG will complete 2 additional appointments with a different nurse performing the measurements. The first one will occur 7 days from the baseline in which the application will be explained and the second one will be during a phone call 15 days from the baseline visit to answer any questions on how to use the application.

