### Primary and secondary outcomes

2.6

The primary outcome will be weight loss (kg). Secondary outcomes will include change in the physical activity (steps/d) measured by accelerometer, sitting time (min/wk), caloric intake (kcal/d), quality of life, arterial aging, and pro-inflammatory markers. All outcomes will be measured at baseline, 3, and 12 months after randomization.

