#### Specific intervention (IG)

2.7.2

The IG will be lent a smartphone and a smartband (Xiaomi Miband 2), for a 3-month period, corresponding to the length of the intervention. A baseline visit will be completed, lasting approximately 15 minutes, in which the subjects will be trained to use the device and the application (EVIDENT 3 Application, [record entry no. 00/2017/2438]) specifically designed for the study (Fig. 2). In the first part of this visit, the application will be configured with each participant's data (sex, age, weight, and height). The application design allows for full daily control of food intake and physical activity performed (more details in Supplementary Material). The application collects the information gathered by the smartband on physical activity, calories, number of steps, number of hours walking, and the information gathered by the subject on daily food intake. Once all the daily information is collected, the application integrates the data to create, based on the subject's characteristics, personalized recommendations, and specific objectives and goals for weight loss. A new visit will take place the week the device is provided, to confirm it is being used properly and to answer any questions. At the 3-month visit, the devices will be collected. All information generated by the application will be duly analyzed and entered in the database. We will evaluate the usability and acceptability of the application^[60]^ after completing the 3-month assessment visit only for IG subjects. A questionnaire will be used to evaluate the application's ease of use, need for training by expert personnel, level of complexity, and its consistency.

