### Analysis of intervention effect in primary and secondary outcomes

2.9

To analyze the changes, at 3 and 12 months from baseline, in primary (weight loss) and secondary endpoints within the same group, we will use the paired *t* test or McNemar test for quantitative or dichotomy variables, respectively.

To analyze the effect of the intervention, we will compare the changes from baseline observed between the IG and CG in weight (primary endpoint) and secondary endpoints, using ANCOVA at 3 and 12 months, adjusting for baseline measures of each variable.

In order to analyze the group effect in the follow-up for primary and secondary endpoints, we will perform a multivariate analysis of the variance of repeated measures, adjusted by the baseline value of each variable. Any interaction between the primary and secondary endpoints with the group (IG vs CG) and Cohen *d* will be estimated.

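### The 3-month comparison of caloric intake uses a questionnaire about the previous year, so about three quarters of the recalled period predates the intervention and any effect is diluted toward zero

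*Protocol article*

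**What the plan says.** - **Outcome.** Section 2.6 of the protocol article lists the secondary outcomes, among them "sitting time (min/wk), caloric intake (kcal/d), quality of life, arterial aging, and pro-inflammatory markers". On timing it says "All outcomes will be measured at baseline, 3, and 12 months after randomization".
- **Instrument.** Section 2.6.4: "Caloric intake (kcal/d) and dietary habits of participants will be evaluated using a semi-quantitative food-frequency questionnaire previously validated in Spain". Its reference period follows: "The estimated frequency corresponds to the previous year at the time of the interview". No different period is given for the follow-up visits.
- **Intervention.** Section 2.7.2 lends the devices "for a 3-month period, corresponding to the length of the intervention". Section 2.5 places the training visit one week in: "The first one will occur 7 days from the baseline in which the application will be explained".
- **Analysis.** Section 2.9 plans within-group paired tests ("To analyze the changes, at 3 and 12 months from baseline, in primary (weight loss) and secondary endpoints") and a between-arm comparison of change "using ANCOVA at 3 and 12 months, adjusting for baseline measures of each variable".

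**The concern.** Each statement is reasonable alone, but together they do not fit. A one-year questionnaire given 3 months after baseline asks mostly about diet before the trial began. Those earlier months were also covered by the baseline questionnaire, so most of the recalled period is common to both interviews. Adjusting for baseline does not repair this, because the dilution is in the follow-up measurement itself.

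The other behavioural outcomes do not have this problem. Sections 2.6.2 and 2.6.3 measure physical activity and sitting time over 7 days, which suits a 3-month visit. Diet is one of the two behaviours that the application targets. At stake is whether a small or null 3-month difference in kcal/d can be told apart from an effect of the recall window.

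**Working it through.** **Inputs from the article:** recall window 12 months (2.6.4); visits at 0, 3 and 12 months (2.6); intervention 3 months (2.7.2); app training on day 7 (2.5).

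**The plan's own figure.** The article gives no figure for the overlap between recall window and intervention. Its one computed figure is the sample size for weight (2.3): difference 3 kg, SD 12 kg, α 0.05 (two-sided assumed), power 80%, loss 15%.
- n per group = 2 × (1.960 + 0.842)² × 12²/3² ≈ 251.2
- 251.2/0.85 ≈ 295.5, rounded up to 296, or 592 in total, as stated. Rounding up to 252 before allowing for loss gives 297 and 594.

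This calculation does not involve kcal/d, so the point does not touch it.

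**Share of the window before the intervention at 3 months.**
- From baseline: (12 − 3)/12 = 75%
- From day 7: (365.25 − 91.3 + 7)/365.25 = 76.9%
- Remaining share: 25%, or 23.1% from day 7

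**Size of the dilution.** If reported intake is a true average over the year, a sustained difference D starting at baseline appears as 0.25 × D. The article gives no expected D, so these values are assumptions:

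| True difference (kcal/d) | Apparent difference at 3 months (kcal/d) |
|---|---|
| 100 | 25 |
| 200 | 50 |
| 300 | 75 |

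If participants in effect give weight w to the last 3 months, the apparent difference is w × D. Literal recall is w = 0.25. For an assumed 200 kcal/d, w = 0.50 gives 100 and w = 0.75 gives 150. Dilution disappears only if w = 1, which means ignoring the stated reference period.

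**Precision, first with unchanged SD.** The required n is multiplied by 1/0.25² = 16. A comparison with 80% power for the full effect has expected z = 1.960 + 0.842 = 2.802. Diluted, this is 0.25 × 2.802 = 0.700, and power is Φ(0.700 − 1.960) ≈ 10%.

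**Precision, allowing for the overlap.** The baseline window covers months −12 to 0 and the 3-month window covers −9 to 3. The shared months −9 to 0 cancel in the change score, leaving

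0.25 × (intake in months 0 to 3 − intake in months −12 to −9) + reporting errors.

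Assume independent quarterly intakes with variance s² and reporting-error variance e² per interview.
- One-year windows: variance of change = 0.0625 × 2s² + 2e²; effect = 0.25 × D
- 3-month windows at both visits: variance of change = 2s² + 2e²; effect = D
- Ratio of required n = (2s² + 32e²)/(2s² + 2e²)

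| Reporting error | n multiplier |
|---|---|
| e = 0 | 2/2 = 1 |
| e = s | 34/4 = 8.5 |
| e much larger than s | approaches 32/2 = 16 |

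This is a change-score calculation. The planned ANCOVA would give somewhat different values, so it should be read as a range.

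**12 months.** The window runs from month 0 to month 12, so none of it predates baseline. It pools about 3 months with the app (3/12 = 25%) and about 9 without it.

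**The case against.** **The dilution may be smaller than 25% suggests.** This stands. People asked about a year may lean on recent eating. The 25% is the literal-recall case, not a measured property of this trial, but the direction stays toward no effect.

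**A reader might infer that the comparison needs 16 times the sample.** The document does not support that as a general statement. It requires the SD of change to stay the same, whereas the overlapping windows shrink true variation in change along with the effect. With negligible reporting error the multiplier is about 1, although the kcal/d estimate is still diluted. The trial is sized on weight alone, so there is no planned n for kcal/d to multiply.

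**A reader might infer that the 12-month comparison fails too.** It does not. Average intake over the follow-up year is a valid between-arm quantity, and the article nowhere says that the questionnaire will test for a return to baseline intake. It needs only the right label.

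**A reader might infer that the trial will conclude that the app leaves diet unchanged, or that weight loss came from activity alone.** The article specifies no mediation analysis that would draw this conclusion, and kcal/d is not its only dietary information. Section 2.6.4 adds the 14-point Mediterranean diet score (MEDAS), and sections 2.7.2 and 2.12 add the app's food records. Neither replaces the 3-month kcal/d comparison, however: MEDAS does not measure kcal, and the app records exist only in the intervention group.

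**The article is condensed.** Follow-up instructions with a shorter window could exist in a fuller document. None is stated, and the only reference period given is tied to the time of each interview.

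**Conclusion.** The point holds for the 3-month kcal/d comparison. As written, 75% of the recalled period (about 77% from day 7) predates the intervention, and no other kcal measure is available in both arms. A sustained difference would appear at about 25% of its size under literal recall, and at a larger fraction if recent diet weighs more. The cost in precision lies between about 1-fold and 16-fold in n, depending on how large reporting error is relative to true variation in intake. The 12-month comparison remains valid as a yearly average. Because the outcome is secondary, and weight and its sample size are untouched, this should be corrected but does not threaten the trial's main result.

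**What to change.** **Preferred.** In section 2.6.4, set the questionnaire's reference period to the last 3 months at baseline, 3 and 12 months, in both arms. Baseline must be included. Otherwise the within-group paired tests in section 2.9 would compare a year with a quarter. At the 3-month visit the window would then fall wholly after baseline, and (91.3 − 7)/91.3 ≈ 92% of it after app training.

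**Cost.** One instruction line on the form, and a departure from the validated one-year window. Seasonality also enters. It is balanced between arms by randomization but affects within-group changes, chiefly at 3 months, since the baseline and 12-month windows would cover the same calendar months.

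**If the validated wording must stay, or baseline data are already collected.** State in sections 2.6.4 and 2.9 that the 3-month kcal/d comparison is diluted by the recall window, and do not interpret it as the intervention effect. Make 12 months the kcal/d comparison, labelled as average intake over the follow-up year. Use MEDAS only as supporting information on diet quality, after confirming its recall period, which the article does not give. It is not a substitute for kcal/d. This route needs no new data, but gives up an interpretable short-term result for energy intake.

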#### Quality of life

2.6.5

Quality of life will be measured using the IWQoL-Lite (Impact of Weight on Quality of Life-Lite). This questionnaire is made up of 31 self-reported items, each of which is scored between 1 (“never true”) and 5 (“always true”). Specific scores are obtained in 5 domains: physical function (11 items), self-esteem (7 items), sexual life (4 items), public distress (5 items), and work (4 items). Higher scores are associated with better quality of life. The original version proved to have good internal consistency (≥0.90), test–retest reliability (≥0.83), and sensitivity to change.^[53]^

#### Arterial aging

2.6.6

The central and peripheral augmentation index will be measured using a novel wrist-worn device developed by Microsoft Research. Participants will be examined in a seated position after 10 minutes of rest. The subject's arm will be supported on a firm surface at heart-height. The wrist-worn device non-invasively senses multiple physiological signals associated with cardiovascular health. The device includes an applanation tonometer placed over the radial artery, an electrocardiogram, a 3-axis accelerometer, and a 3-axis gyroscope. It is capable of performing continuous or scheduled measurements using various configurations of these sensors and it includes Bluetooth for data streaming.^[54]^ Cardio-ankle vascular index (CAVI), brachial-ankle pulse wave velocity (ba-PWV), and ankle-brachial index (ABI) will be measured at rest, using the Vasera device VS-2000 (Fukuda Denshi).

#### Pro-Inflammatory markers

2.6.7

A centralized laboratory will measure levels of IL-1β, IL-7, and adiponectin, as they are considered pro-inflammatory markers related to obesity.^[55]^ Venous blood sampling will be performed between 8:00 am and 9:00 am after participants have fasted and abstained from smoking, consumption of alcohol, and caffeinated beverages for 12 hours. Other laboratory determinations, such as plasma glucose, creatinine, total serum cholesterol, high-density lipoprotein (HDL) cholesterol, low-density lipoprotein (LDL) cholesterol, and triglyceride concentrations will be determined using standard automated enzymatic methods. Glycosylated hemoglobin, high-sensitivity C-reactive protein levels, insulinemia, and fibrinogen values will be measured with an immune-turbidimetric assay. An ELISA will be used to determine the levels of thyroid-stimulating hormone (TSH) and free T4 hormone. Spot morning urine samples will be collected to determine the albumin–creatinine ratio. The analyses will be performed at the hospitals in the cities participating in external quality assurance programs of the Spanish Society of Clinical Chemistry and Molecular Pathology.

#### Other variables

2.6.8

Sociodemographic variables: At the time of inclusion in the study, data on age, sex, marital status, educational level, and occupation will be collected.

Peripheral blood pressure: Three measurements of systolic (SBP) and diastolic (DBP) blood pressure will be performed using the average of the last 2 with a validated Omron M10-IT model sphygmomanometer (Omron Healthcare, Kyoto, Japan). The measurements will be made on the participant's dominant arm in a seated position after at least 5 minutes of rest with a cuff of appropriate size, as determined by measurement of the upper arm circumference and following the recommendations of the European Society of Hypertension.^[56]^

Smoking status: This will be assessed through a questionnaire of 4 standard questions adapted from the WHO MONICA study.^[57]^ Study participants will be classified as current smokers or non-smokers (never or >1 year without smoking).

Motivation to change: We will use the motivation stage according to the transtheoretical model of change (TTM)—Prochaska and DiClemente model (pre-contemplation, contemplation, preparation, action, maintenance, and relapse).^[58]^ TTM constructs will be measured only when relating to weight loss.

### Intervention

2.7

#### Standard counselling (CG and IG)

2.7.1

Both groups (control and intervention) will receive 5 minutes of counselling at the end of the baseline visit and prior to randomization. Advice on physical activity will be in compliance with the current international recommendations for the general population. The health benefits of physical activity and the recommendation to complete at least 30 minutes of moderate activity 5 days a week, or 20 minutes of vigorous activity 3 days a week, will be explained. Counselling on food will be in compliance with the plate method,^[59]^ in which a plate is divided into 4 parts: half the plate for salad or vegetables, one fourth for proteins (white meat preferred over red meat), and the final fourth for carbohydrates. In addition, a medium-sized piece of fruit and a skimmed dairy product should be consumed for dessert.

#### Specific intervention (IG)

2.7.2

The IG will be lent a smartphone and a smartband (Xiaomi Miband 2), for a 3-month period, corresponding to the length of the intervention. A baseline visit will be completed, lasting approximately 15 minutes, in which the subjects will be trained to use the device and the application (EVIDENT 3 Application, [record entry no. 00/2017/2438]) specifically designed for the study (Fig. 2). In the first part of this visit, the application will be configured with each participant's data (sex, age, weight, and height). The application design allows for full daily control of food intake and physical activity performed (more details in Supplementary Material). The application collects the information gathered by the smartband on physical activity, calories, number of steps, number of hours walking, and the information gathered by the subject on daily food intake. Once all the daily information is collected, the application integrates the data to create, based on the subject's characteristics, personalized recommendations, and specific objectives and goals for weight loss. A new visit will take place the week the device is provided, to confirm it is being used properly and to answer any questions. At the 3-month visit, the devices will be collected. All information generated by the application will be duly analyzed and entered in the database. We will evaluate the usability and acceptability of the application^[60]^ after completing the 3-month assessment visit only for IG subjects. A questionnaire will be used to evaluate the application's ease of use, need for training by expert personnel, level of complexity, and its consistency.

**Figure 2 F2:**
[figure not shown]
Screenshots of the EVIDENT 3 application.

#### Blinding strategy

2.7.3

The investigator carrying out the intervention with the IG will be different from the person responsible for the assessment and the standard counselling; both will be kept blinded throughout the study, as will the investigator conducting the data analysis. The subjects, due to the nature of the study, cannot be blinded. To prevent contamination between groups, in the assessment visits (3 and 6 months), only the study variables will be evaluated but no advice or reinforcement will be given. In addition, the application will not be available for download on the web until the end of the study so the CG will not be able to make use of it in any way. During the follow-up visits, participants will be instructed not to use other health technologies. Compliance will be ensured by a brief question about the use of other applications and mHealth technology.

### Statistical analysis

2.8

#### General analysis

2.8.1

Results will be expressed as mean ± standard deviation for quantitative variables normally distributed or medians (interquartile ranges) for the skewed variables and by frequency distribution for qualitative variables. The statistical normality will be tested using the Kolmogorov–Smirnov test. The Chi-square test and Fisher exact test will be used to analyze the association between independent qualitative variables. The Student's *t* test or Mann–Whitney *U* test will be used for the comparison of means between 2 independent groups. Pearson correlation or Rho de Spearman will be used to evaluate the relationships between quantitative variables.

The main analysis of primary and secondary outcomes will be performed on an intent-to-treat basis. We will also perform a secondary analysis according to the different levels of adherence to the use of the application (low adherence: <2 months; high adherence: ≥2 months) and according to relevant subgroups. Multiple imputations will be used to address missing values in the dataset.

### Analysis of intervention effect in primary and secondary outcomes

2.9

To analyze the changes, at 3 and 12 months from baseline, in primary (weight loss) and secondary endpoints within the same group, we will use the paired *t* test or McNemar test for quantitative or dichotomy variables, respectively.

To analyze the effect of the intervention, we will compare the changes from baseline observed between the IG and CG in weight (primary endpoint) and secondary endpoints, using ANCOVA at 3 and 12 months, adjusting for baseline measures of each variable.

In order to analyze the group effect in the follow-up for primary and secondary endpoints, we will perform a multivariate analysis of the variance of repeated measures, adjusted by the baseline value of each variable. Any interaction between the primary and secondary endpoints with the group (IG vs CG) and Cohen *d* will be estimated.

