### Sample size

2.3

The sample size calculation was performed for the primary study endpoint of weight loss. Accepting an α risk of 0.05 and a β risk of 0.20, with an standard deviation (SD) of 12 kg, estimated in subjects from EVIDENT 2 study,^[35]^ 592 subjects would be needed (296 per group) to detect a decrease in weight of ≥3 kg^[39]^ in the intervention group (IG) versus the control group (CG), taking into consideration a 15% loss to follow-up. This effect size represents a 3% to 5% difference between groups, which should produce clinically relevant health benefits.^[40]^ To minimize dropouts, a reminder of the next visit will be provided at the end of each visit, as well as 2 phone calls 15 and 5 days prior.

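### Weight loss, the only primary outcome, has no deciding time point, yet it is tested between groups at both 3 and 12 months at the full 5% level

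*Protocol article*

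**What the plan says.** - **Outcome (2.6).** Weight loss in kg is the primary outcome. No visit is attached to it: "All outcomes will be measured at baseline, 3, and 12 months after randomization". The objective at the end of 1.5 gives no time either.
- **Sample size (2.3).** "Accepting an α risk of 0.05 and a β risk of 0.20", "with an standard deviation (SD) of 12 kg", the trial is sized "to detect a decrease in weight of ≥3 kg" in the intervention group relative to control, "taking into consideration a 15% loss to follow-up". The result is "592 subjects would be needed (296 per group"). The text does not say at which visit the 3 kg applies.
- **Analysis (2.9).** Changes in weight, labelled there as the primary endpoint, are compared between groups "using ANCOVA at 3 and 12 months, adjusting for baseline measures of each variable". For the group effect over follow-up, "we will perform a multivariate analysis of the variance of repeated measures, adjusted by the baseline value of each variable".
- **Significance level (2.12).** One threshold, P at or below .05, is set for all analyses.
- **Intervention (2.7.2).** The phone and smartband are lent for three months and collected at the 3-month visit.
- **Status of the visits (2.11).** Three months is called short term and 12 months long term, in the comparison of men and women. Neither is ranked above the other.

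**The concern.** Two ANCOVAs and one repeated-measures test address the same primary endpoint, each at 0.05. No order, alpha split or both-must-succeed rule is given, so the primary conclusion could rest on whichever visit is significant.

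The choice of visit changes the claim. At 3 months the comparison measures the effect at the end of app use. At 12 months it measures what remains nine months after the devices went back (12 − 3 = 9). An effect seen only at 3 months could be reported as a positive trial, and so could one seen only at 12 months. The protocol gives no rule for saying which of these meets the primary objective. The same gap leaves the chance of a false-positive primary claim undefined, although the trial was sized for a single test.

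**Working it through.** **Step 1: reproduce the sample size.** Inputs from 2.3: difference 3 kg, SD 12 kg, alpha 0.05, power 1 − 0.20 = 0.80, loss 15%.

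n per group = 2 × [SD × (z for alpha + z for power) / difference]²

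- Two-sided: 2 × [12 × (1.960 + 0.842) / 3]² = 251.2. Dividing by 1 − 0.15 gives 251.2 / 0.85 = 295.5, so 296 per group and 592 in total. This matches the protocol.
- One-sided: 198 per group, and 198 / 0.85 gives 233 per group. This does not match.

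The stated size therefore corresponds to one two-sided test at 0.05.

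**Step 2: false-positive risk if either ANCOVA may count.** With no true effect at either visit, let Z1 and Z2 be the 3- and 12-month test statistics with correlation r.

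Risk = 1 − P(|Z1| < 1.96 and |Z2| < 1.96)

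If the tests were independent this is 1 − 0.95² = 0.0975. The document gives no value for r, so it is an assumption shown as a range. The ANCOVA-only column below is exact (bivariate normal).

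**Step 3: add the stated repeated-measures group test.** The protocol does not say which form this test takes, so two readings were simulated (2 million draws for each r): a test of the average effect over the two visits, and a joint test with 2 degrees of freedom.

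| Assumed r | Either ANCOVA | Plus average-effect test | Plus 2-df joint test |
|---|---|---|---|
| 0.5 | 9.1% | 9.7% | 9.9% |
| 0.7 | 8.4% | 8.6% | 9.6% |
| 0.8 | 7.8% | 8.0% | 9.3% |
| 0.9 | 7.0% | 7.1% | 8.9% |
| 0.95 | 6.5% | 6.5% | 8.5% |

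The two ANCOVAs alone exceed 5% at every correlation below 1. The average-effect reading adds little to them. The joint reading adds more when r is high.

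**Step 4: cost of keeping both visits as alternative routes to success.** A Bonferroni split tests each at 0.025.

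- Size needed: 2 × [12 × (2.241 + 0.842) / 3]² gives 305 evaluable per group after rounding up. 305 / 0.85 gives 359 per group, or 718 in total.
- Power at the planned size: 296 × 0.85 = 251.6 evaluable per group. The expected test statistic is 3 / (12 × √(2 / 251.6)) = 2.80, and 2.80 − 2.24 = 0.56, so power per test is about 71% instead of 80%.

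The within-group paired tests in 2.9 are not counted, because they do not compare the groups.

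**The case against.** **The inflation is conditional.** The protocol states no rule that either visit suffices. If both visits had to be significant, alpha would not be inflated, and 2.3 uses 0.05 for sizing without claiming family-wise control. This stands. A reader might infer that the 5% level is certainly not met, but the document does not support that. What it supports is that the deciding visit is undefined, so error control cannot be established.

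**The inflation may be modest.** Adjusted weights at 3 and 12 months could be highly correlated, and at r = 0.95 the figure for the ANCOVAs is 6.5%. This also stands, and the range is shown for that reason.

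**A larger figure is tempting.** A reader might treat a group-by-time contrast as a further route to success, which would bring the total to about 12% to 13% for r from 0.8 to 0.5. The protocol does not state such a test. Section 2.9 says only that an interaction involving the endpoints and group will be estimated. A group-by-time contrast would also ask whether the effect changes between visits, not whether the app works. The figure is not used here.

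**This could be left to an analysis plan.** Details such as gatekeeping order often are. But the article itself fixes two test times for the primary endpoint, adds a third test, sets the full level for all of them and sizes for one test. The time of the primary endpoint is part of its definition. This objection does not remove the point.

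**The repeated-measures method is not shown to be wrong.** Replacing it with a mixed model would be a preference, and is not asked for.

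**Conclusion.** The point holds in this form: the primary outcome has no deciding visit, and two between-group ANCOVAs plus a repeated-measures group test are planned on it at 0.05, while the trial is sized for one such test. If either visit may count as success, the chance of at least one false-positive ANCOVA is about 6.5% to 9.1% for r from 0.95 to 0.5, with 9.75% under independence. Including the stated repeated-measures test, it is about 6.5% to 9.9% over the same range of r, depending on which form that test takes.

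These figures rest on the assumed correlation and on the either-visit reading. The ambiguity about which question is primary, end of intervention or persistence, does not depend on either assumption. The sample size calculation is correct and needs no change once one visit, or a fixed order, is named.

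**What to change.** Before unblinding, and consistently in 2.3, 2.6 and 2.9, do one of the following:

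1. Name one deciding ANCOVA for weight, at 3 or at 12 months as the sponsor chooses, and make the other visit secondary.
2. Fix an order of the two ANCOVAs, again the sponsor's choice, in which the second visit is tested at two-sided 0.05 only if the first is significant.

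In either case, state in 2.3 the visit to which the 3 kg applies, and label the repeated-measures analysis supportive. As a minor wording correction, the interaction in 2.9 should read group by time, because the endpoints are responses in that model and not factors.

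The cost is wording only, with no extra participants, and N stays at 592. The downside is small: the other visit becomes secondary under option 1, or confirmatory only if the first succeeds under option 2. By comparison, keeping both visits as alternative routes to success with a Bonferroni split would need 718 participants, or would accept about 71% power per test with 592.
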